#### Participant recruitment

Patients are recruited by the participating urologists of 15 hospitals throughout Belgium (Flanders and Brussels) from September 2009 to August 2012. All subjects have to master the Dutch or French language and may be excluded due to illness, mental sickness or incapacity to comprehend the questions as evaluated by the treating clinician. Eligible patients receive oral and written information (information brochure) from the research nurse and sign an informed consent form. The procedures followed are in accordance with the ethical standards of the responsible committee on human experimentation (institutional and national) and with the Helsinki Declaration of 1975, as revised in 2008. The study has been approved by the ethical review board of the University Hospital of Leuven acting as the central ethical review board, by the trial steering committee and by the appropriate ethical review boards related to the hospitals in which it is performed. A Data Safety Monitoring Board (DSMB), comprised of individuals with expertise in the areas of medicine and biostatistics, has been established to serve as an external review committee to monitor the progress of the study including accrual and adverse events.

#### Randomization

Randomization is stratified by treatment centre. Once a patient is deemed to be eligible for the trial and has given written consent, a trained research nurse randomizes the patient by using the database. A computerized algorithm randomly assigns the patients to a treatment arm. All study personnel and participants are blinded to treatment assignment for the duration of the study. To evaluate patient blinding, patients are asked by a questionnaire to evaluate which treatment they believe they have received (selenium, placebo, or don't know). If patients answer either selenium or placebo, they are asked to indicate what led to that belief.

#### Participant follow-up

Study participants are supplied with the study drug and followed on a bi-annual basis for a period of up to three years. This follow-up phase entails questionnaire distribution and monitoring for adverse events. Study questionnaires capture the onset of new illnesses and symptoms, including potential selenium-related toxicities.

#### Investigational medicinal product (IMP)

The active product is selenium (200 μg/day, in the form of high-selenium yeast, SelenoPrecise from PharmaNord, Vojens, Denmark). A six-month intake of 200 μg of SelenoPrecise yeast increases the plasma selenium levels on average from a baseline value of (mean ± SD) 92 ± 20 ng/mL to 196 ± 42 ng/mL. The increase of the plasma selenium level is dose-dependent [29]. Patients in each study arm received an oral tablet (selenium or placebo) to be taken daily, in addition to standard care. Standard care is provided as described by Oosterlinck in the "Guidelines on diagnosis and treatment of superficial bladder cancer" [30]. Placebos have been manufactured to be identical in appearance, smell and taste to the active agents. They were identical in their composition except for the active agents. The duration of the treatment in both arms is three years, in absence of concurrent illness that prevents further administration of treatment, an unacceptable adverse event, an unacceptable toxicity or if a patient decides to withdraw from the study. Treatment stops if general or specific changes in the patient's condition render the patient ineligible for further treatment in the judgment of the investigator or the treating physician.

#### Drug interactions/precautions

There are no known contra-indications, interactions or precautions for the use of selenium. A few individuals are allergic to yeast for whom this form of supplement would clearly be unsuitable, but this is not a common problem [19]. Known adverse health effects of selenium concern the synthesis of thyroid hormones (diminished T3 level), hepatotoxicity, gastrointestinal disturbances, nail and hair loss and dermatitis. However these symptoms have been associated with selenium intakes of more than 700 μg a day [31].

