#### Eligibility criteria for participants

Men and women, at least 18 years of age, who give informed consent, are eligible for inclusion in SELEBLAT, if they have undergone a transurethral resection (TUR) of a histologically confirmed transitional cell carcinoma of the bladder, stage pTa, pT1 or Carcinoma in situ (Cis). Primary and second primary tumours are included. Eligibility and exclusion criteria are:

• Men and women, aged above 18 years

• Histologically confirmed non-muscle-invasive transitional cell carcinoma (< pT2): stage pTa, pT1 or Carcinoma in situ (Cis)

• Primary and second primary tumours

• Able to be randomized within three months after transurethral resection of the bladder tumour

• Must be able to swallow pills

• Must agree not to take supplements containing selenium, apart from the trial medication

• Fertile female patients must use effective contraception

• No invasive or metastatic disease (stage pT2 or above)

• No history of any type of malignancy within the past five years

• No other serious medical or psychiatric illness that would preclude giving informed consent

• No known hypersensitivity or adverse reactions to selenium

• Not taking more than 50 mg selenium/day as a dietary supplement, including multivitamin supplements within the last 30 days

• Not concurrently participating or having participated in any other clinical trial involving a medical, surgical, nutritional or life-style intervention (unless no longer receiving the intervention and being in the follow-up phase)

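### The eligibility criteria exclude known hypersensitivity to selenium but not to yeast, although the study product is a selenium yeast that the article calls unsuitable for people allergic to yeast

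*Protocol article*

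**What the plan says.** Four parts of the Methods bear on the point.

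- **Product.** Investigational medicinal product (IMP) gives the active treatment as 200 μg of selenium per day "in the form of high-selenium yeast", taken for three years.
- **Precaution.** Drug interactions/precautions first reports no known contra-indications for selenium. It then says of the yeast form: "A few individuals are allergic to yeast for whom this form of supplement would clearly be unsuitable". It adds that the problem is not common.
- **Criteria.** Eligibility criteria for participants introduces its list with "Eligibility and exclusion criteria are" and prints 13 items. The one item on allergy is "No known hypersensitivity or adverse reactions to selenium".
- **Entry to the trial.** Participant recruitment adds that subjects "may be excluded due to illness, mental sickness or incapacity to comprehend the questions as evaluated by the treating clinician". Randomization then states: "Once a patient is deemed to be eligible for the trial and has given written consent, a trained research nurse randomizes the patient".

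After randomisation, the IMP section lets treatment stop for several reasons, among them "an unacceptable adverse event, an unacceptable toxicity or if a patient decides to withdraw from the study".

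**The concern.** The article names a group of people who should not take this form of selenium, but it prints an allergy criterion that does not cover them. The criterion is about the element, while the stated hazard is about the carrier. A nurse or urologist who works through the list item by item has no prompt to ask about yeast, and a patient who knows of such an allergy passes every item.

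What is at stake is the safety of those few patients. They could be given a daily tablet for up to three years that the plan itself regards as wrong for them. No estimate or test in the trial depends on it.

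**Working it through.** No formula applies, and the plan gives no figure to reproduce. The check sets the sections side by side.

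1. **What is the product?** The IMP section says selenium in a yeast form. Yeast is part of the active treatment.
2. **Is yeast allergy recognised as a hazard?** Yes, under Drug interactions/precautions, in the words "A few individuals are allergic to yeast for whom this form of supplement would clearly be unsuitable". The preceding sentence clears selenium of contra-indications, so the section treats selenium and its yeast carrier as two separate matters.
3. **Does the eligibility list carry the hazard over?** Of the 13 printed items, 1 concerns hypersensitivity ("No known hypersensitivity or adverse reactions to selenium") and 0 name yeast.
4. **Is the list presented as a selection?** It opens with "Eligibility and exclusion criteria are" and does not call its items the key or main criteria. It goes down to such details as the ability to swallow pills, contraception and supplement use in the preceding 30 days. It includes an allergy item, so the topic has been addressed. What falls short is how that item is worded.
5. **Does another section close the gap before randomisation?** Participant recruitment allows exclusion for illness on the clinician's judgment, but the wording is permissive ("may be excluded due to illness, mental sickness or incapacity to comprehend the questions as evaluated by the treating clinician") and does not mention allergy. The Discussion describes a policy of including the patients undergoing resection who meet the criteria, and of not excluding for co-morbidity or age. Under that policy the wording of the criteria largely decides who enters.
6. **Does a later safeguard close it?** The stopping reasons in the IMP section ("an unacceptable adverse event, an unacceptable toxicity or if a patient decides to withdraw from the study") take effect only once tablets have been supplied. They limit harm but do not prevent exposure.
7. **Which arm would the patient receive?** Either. The IMP section says the placebo matches the active tablet except for the active agent. If that agent is the selenium alone, both tablets may contain yeast. If it is the selenium yeast, only the active tablet does. The article does not settle this, so exposure is possible for such a patient but not certain.

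The criteria as printed therefore admit a group that the same document says should not take the product.

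**The case against.** The strongest case on the other side has three parts.

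First, this is a condensed article. The full protocol is not shown and may name yeast, and the article does state the precaution correctly in its Methods. It is true that the full protocol could contain such an item. But the article did not leave the allergy criterion to another document: it printed one, and the printed one is incomplete against its own precaution.

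Second, the list is not closed. Participant recruitment adds a language requirement and clinician discretion that are not among the 13 items, so eligibility conditions do sit elsewhere. This stands as far as it goes, and a careful clinician may well act on the precaution. The discretion is optional, however, and no section turns yeast allergy into a criterion.

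Third, the article often uses selenium as shorthand for the trial product, for instance when it describes the tablet as selenium or placebo. On that usage the hypersensitivity item could be read as covering the product, and a past reaction to selenium yeast would be caught. That reading is possible. It is weakened by the precautions section, which separates selenium from its yeast form, and it would not clearly cover someone who has reacted to yeast but never taken selenium yeast.

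A reader might also infer that everyone recruited so far, or still to be recruited, is in some sense at risk. The documents do not support that: recruitment totals do not measure how many people have a yeast allergy, and no prevalence is given. Nor do they support the inference that every such patient would receive yeast, for the reason in step 7 of the working.

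**Conclusion.** The point holds as a minor patient-safety defect in the eligibility wording. A patient with a known yeast allergy satisfies the printed criteria and can be randomised, with possible assignment to a product that the article calls unsuitable for that patient.

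Its size cannot be computed. The article offers only that a few individuals are affected and that the problem is uncommon, so the frequency is unknown but presumably small. Sample size, the primary endpoint and the analysis are not affected.

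The conclusion rests on two assumptions: that the printed list is what recruiting staff apply, and that the word selenium in the hypersensitivity item means selenium and not the whole product. If the full protocol already names yeast, only the article's wording needs correcting.

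A reader might infer that patients already randomised should now be questioned about yeast allergy and taken off the tablets under the existing physician-judgment rule. The documents do not support that step. That rule in the IMP section is triggered by a change in the patient's condition, and a pre-existing allergy is not a change. Patients already taking tablets are monitored for adverse events, and the routes for an unacceptable adverse event or for withdrawal remain open to them.

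**What to change.** For patients still to be recruited, make two edits:

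- In Eligibility criteria for participants, extend the item "No known hypersensitivity or adverse reactions to selenium" by adding the words 'or yeast' at its end.
- In Drug interactions/precautions, list known yeast allergy as a contra-indication to the study product, so that the precaution and the criterion agree.

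The cost is a small eligibility amendment during recruitment and the loss of a few patients, all from the group for whom the article already calls the product unsuitable. The reworded item catches only allergy that the patient already knows about. The sample size and the analysis need no change.

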#### Safety and toxicity

Data on toxicity of selenium yeast are available from two animal studies while a number of human intervention studies show that the chronic administration of Se-yeast up to 800 μg/d provides no evidence of toxicity [19].

In 2008 there was an outbreak of selenium toxicity (selenosis). The source was identified as a liquid dietary supplement that contained 200 times the labelled concentration of selenium in the form of sodium selenite. Of 201 cases identified in ten states in the US, one person was hospitalized. The median estimated dose of selenium consumed was 41749 μg/day. Frequently reported symptoms included diarrhoea (78%), fatigue (75%), hair loss (72%), joint pain (70%), nail discoloration or brittleness (61%), and nausea (58%) [32]. It is suggested that hair, fingernails and toenails may all act as excretory organs when excess amounts of selenium are ingested [33]. The Food and Nutrition Board-Institute of Medicine [34] fixed the highest daily level of selenium that is likely to pose no risk of adverse health effects in almost all individuals at 400 μg selenium per day [31].

#### Compliance and drug accountability

The message of compliance is repeated during each follow-up visit. Patients are encouraged to return unused medication and empty packs. In order to check compliance, the research nurse counts and records the remaining unused tablets during each follow-up visit. Unused medication is collected and destroyed by PharmaNord.

#### Data collection

Patients receive a self-completion questionnaire after TUR, comprising questions about socio-demographics (age, sex, ethnicity, marital status, education) health-related lifestyle (lifetime smoking, history, passive smoking), medical and drug history, dietary intake (food-type frequency, alcohol, caffeine and total fluid intake, use of vitamins), social support and quality of life. The quality-of-life questions were developed by the European Organization for Research and Treatment for Cancer (EORTC). Assessments using the general cancer questionnaire QLQ-C30 and the QLQ-BLS24, with 24 supplemental questions, are made at baseline, after 6 and 36 months. A full version of the baseline and the follow-up questionnaires is available as a free download at http://www.bcpp.bham.ac.uk/seleblateng/patients.shtml. Patients' medical records are regularly examined by the research nurses for information on clinical treatment, histopathology, and outcome measures, which are reported on case report forms.

Blood samples are collected at baseline. A research nurse collects blood from all patients in a 5-mL EDTA tube for selenium measurement and one plain 10-mL tube for DNA-analysis. After the three-year intervention period a new blood sample for selenium measurement is collected.

#### Adverse event and serious adverse event monitoring strategy

For the purpose of this trial, any detrimental change in the patient's condition subsequent to the start of trial treatment and during the trial follow-up period, which is not unequivocally due to the underlying disease process of bladder cancer, is considered as either an adverse event (AE) or a serious adverse event (SAE). Adverse events and serious adverse events are being monitored during and between regular follow-up visits in accordance with the legal regulations.

#### Statistical analysis

Final statistical analysis is on an intention-to-treat basis. Kaplan-Meier estimates of a recurrence-free interval are used to compare treatment groups descriptively, whilst log-rank tests are used to test the hypothesis of no difference between treatments. Cox proportional hazards regression models are used to estimate the Hazard risks and 95% confidence intervals comparing patients randomized to active selenium versus placebo with and without adjustment for age, sex and stage at time of diagnosis. A per protocol analysis will be performed as a sensitivity analysis. We will also test for interactions with possible additional effect modifiers such as smoking, selenium at baseline as an indicator of selenium intake. For secondary outcome measures, treatment arms are compared in terms of progression-free interval using Kaplan-Meier and log-rank tests. The reasons for excluding patients from the analysis are clearly reported.

All analyzes are performed using STATA (StataCorp. 2009. *Stata Statistical Software: Release 11*. College Station, TX: StataCorp LP)

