#### Sample size calculations

Sample size calculations are based on the recent meta-analysis (N = 2820) by Malström et al. [35] who looked at the recurrence after standard treatment (instillations of mitomycine or BCG). This is the group that corresponds best with our placebo-group (standard care). The absolute difference between the placebo- and the Selenium-group is based on the difference in percent of recurrence after five years (average of time after randomization in our study). A difference of 12,5% in absolute reduction can be expected, considering that the intake of 200 μg of SelenoPrecise yeast increases the plasma selenium by ± 100 ng/mL [29] and that, according to epidemiological studies, the incidence of bladder cancer decreases by 25% if the plasma selenium increases by 10 ng/mL [10].

To detect an absolute decrease of 12,5% in the recurrence-free rate by selenium versus placebo, 700 patients are needed, taking into account a drop out of 25% with a power of 86% (two-sided test).

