#### Baseline characteristics

At the time of writing we have recruited 177 patients. After one year of recruitment, 137 patients were assessed for eligibility of which 100 met the inclusion criteria. All patients were between 46 and 88 years and their mean age was 68 (± 9) years. Eighty-three percent of the patients were male and 87% of them Dutch-speaking. Sixty percent had a primary tumour and 60% had a solitary tumour. Seventy-nine percent of the tumours were papillary. The baseline plasma selenium was 84.8 ng/mL (± 18.5 ng/mL). Baseline characteristics were summarized in Table 1.

**Table 1 T1:** Baseline characteristics of randomized participants in the SELEBLAT trial

Variable		Total 100	
Gender [N (%)]	Male [N (%)]	83	(83)
	Female	17	(17)
Age	≤ 50 yrs. [N (%)]	2	(2)
	51-60 [N (%)]	17	(17)
	61-70 [N (%)]	34	(34)
	71-80 [N (%)]	36	(36)
	> 80 [N (%)]	11	(11)
	Years [mean, (SD)]	68	(9)
Language [N (%)]	Dutch	87	(87)
	French	13	(13)
Primary	Primary	61	(60)
Tumour [N (%)]	Recurrent	35	(35)
	Unknown	5	(5)
Tumour	G1	31	(30)
Grade [N (%)]	G2	35	(34)
	G3	33	(32)
	Unknown	4	(4)
Tumour	pTa	60	(58)
Stage [N (%)]	pT1	31	(30)
	Cis	5	(5)
	Unknown	7	(7)
Tumour	Papillary	121	(79)
Type [N (%)]	Cis	29	(19)
	Unknown	3	(2)
Tumour	< 1 cm	59	(38)
Size [N (%)]	≥1 and ≤ 3	56	(37)
	> 3 cm	38	(25)
Tumour	Solitary	59	(60)
Number [N (%)]	2 or more	36	(36)
	Unknown	4	(4)
Selenium	ng/mL [mean, (SD)]	84.8	(18.5)

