The SELEBLAT study is well-designed. Selenium-yeast is a safe and cheap medicine. A computerized program performs our randomization. Neither the investigators, nor the research nurses have access to the randomization numbers. All study personnel is blinded for the medication. Both treatment groups are regularly compared on similarity of prognostic characteristics such as age, gender, smoking, grade of tumour, baseline selenium level and co-morbidity. We will report reasons and numbers of those patients lost to follow up. Both an intention to treat and a per protocol analysis will be performed. For hypothesis building subgroup analyses and analyses of interactions will be performed, as we have demographic and clinical data and questionnaires results on diet and Quality of Life. Standard treatment will be compared between the intervention and the placebo group. Additional intake of selenium by food supplements will be analyzed and compliance will be reported. Our primary outcome measures are both clinical and histologically confirmed recurrences as frequently patients with clinical recurrence are only cauterized without taking a biopsy. Cauterization only reduces the risk of perforation of the bladder. All subsequent patients undergoing TUR operation are included meeting the inclusion criteria. We decided to include both primary and second primary tumours, because the incidence of bladder cancer is low, while the prevalence and the rate of tumour recurrence is high [24]. Recurrence within the first three months after TUR is considered as residual untreated disease. Although bladder cancer and prostate cancer occur together in 10% of the cases [59,60], we decided to exclude patients with prostate cancer too. We deliberately did not exclude any patient for presence of co-morbidity or age aiming for a study population, which represents as far as possible the normal population diagnosed with bladder cancer. We intend to reach the calculated sample size by pooling of our results with the results from the Selenib study (UK), which is similar in design. Progress of the study can be followed on the website: http://www.genepid.bham.ac.uk/Seleblat_Recruitment.shtml. The first results of our study can be expected for 2014.

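### Randomisation is stratified by centre, but the stated log-rank and Cox analyses do not use centre, the adjusted model lists only age, sex and stage, and no hazard ratio is named as primary

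*Protocol article*

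**What the plan says.** On design, the protocol article (Randomization, and the Abstract) states: "Randomization is stratified by treatment centre". No other stratification factor is named. Participant recruitment gives the number of centres: "Patients are recruited by the participating urologists of 15 hospitals throughout Belgium".

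On analysis, the Statistical analysis section says for the primary endpoint that "log-rank tests are used to test the hypothesis of no difference between treatments". Hazard ratios come from Cox models "with and without adjustment for age, sex and stage at time of diagnosis". For the secondary endpoint, "treatment arms are compared in terms of progression-free interval using Kaplan-Meier and log-rank tests". Centre is mentioned in none of these. Smoking and baseline selenium appear in the same section, but only as possible effect modifiers.

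On what is known at baseline, Table 1 records grade, stage, primary or recurrent status, tumour number and plasma selenium. The accompanying text reports that "Sixty percent had a primary tumour and 60% had a solitary tumour". The Discussion says the arms are regularly compared on "prognostic characteristics such as age, gender, smoking, grade of tumour, baseline selenium level and co-morbidity".

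**The concern.** An analysis normally carries the factor that the randomisation was balanced on. When patients are balanced within centre and centres differ in recurrence, an unstratified log-rank test uses a variance that is too large for the design. It rejects less often than it should, both under the null and under a real effect. Leaving out factors that predict recurrence also moves a Cox hazard ratio toward 1 relative to the within-stratum effect.

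In addition, two hazard ratios are planned and neither ranks first, so the headline estimate could be picked after the data are seen. The remedy uses only data already being collected, and the trial is short of patients: 177 had been recruited at the time of writing against a target of 700.

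**Working it through.** **1. Factors set side by side**

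| Factor | Where it is recorded or used | In the stated Cox adjustment? |
|---|---|---|
| Centre | Stratifies randomisation | No |
| Age, sex, stage | Table 1 | Yes |
| Grade | Table 1; Discussion list | No |
| Primary/recurrent, tumour number | Table 1 | No |
| Baseline selenium | Table 1; Discussion list; interaction test | No (interaction only) |

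**2. The plan's own sample size**

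Sample size calculations: "To detect an absolute decrease of 12,5% in the recurrence-free rate by selenium versus placebo, 700 patients are needed", with 25% drop-out, 86% power and a two-sided test. The control recurrence rate, alpha and allocation ratio are not given. Assume 40% v 27.5%, alpha 0.05 and 1:1, so the mean rate is 0.3375.

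n per arm = [1.960·√(2·0.3375·0.6625) + 1.080·√(0.40·0.60 + 0.275·0.725)]² / 0.125² = (1.311 + 0.716)² / 0.015625 ≈ 263.

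The total is 526, and 526/0.75 = 702. So 700 is attainable and is not disputed here. Evaluable patients: 700 × 0.75 = 525.

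The exponential hazard ratio is ln(0.725)/ln(0.60) = 0.63. A second scenario, 50% v 37.5%, gives ln(0.625)/ln(0.50) = 0.678.

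Check with no centre effect: events = 525 × 0.3375 = 177; power = Φ(√(177/4) × 0.463 − 1.960) = Φ(1.12) ≈ 87%, which agrees with the simulation below.

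**3. Centre alone, 525 patients**

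Assumptions: 15 centres of unequal size, permuted blocks of 4 within centre, exponential times, censoring at 5 years and normally distributed centre log-hazards. There were 4,000 trials per row for 40% v 27.5% (Monte Carlo error about 0.5 points). The last column is a smaller run at 50% v 37.5%. To give a scale, centres one SD above and one SD below average differ in hazard by e^(2·SD): 2.2-fold at SD 0.4 and 5.0-fold at SD 0.8.

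| Centre SD | Power, unstratified v stratified (40%) | HR, unstratified v stratified | Null rejection, unstratified | Power, unstratified v stratified (50%) |
|---|---|---|---|---|
| 0 | 87.0% v 87.1% | 0.627 v 0.627 | 5.0% | 83.4% v 83.3% |
| 0.2 | 85.6% v 85.9% | 0.634 v 0.632 | 5.5% | 83.0% v 83.8% |
| 0.4 | 86.0% v 86.8% | 0.636 v 0.628 | 4.6% | 83.5% v 85.3% |
| 0.6 | 84.5% v 87.5% | 0.648 v 0.628 | 3.8% | 78.5% v 83.2% |
| 0.8 | 82.7% v 88.2% | 0.662 v 0.627 | 3.2% | 76.5% v 84.6% |

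**4. Centre and tumour covariates together, 525 patients**

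Scenario 50% v 37.5%, true HR 0.678. Assumed prognostic hazard ratios: 1.7 (multiple tumours), 1.6 (recurrent), 1.3 (G3). The comparison is unstratified and unadjusted v centre-stratified and adjusted.

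| Simulation | Centre SD | Power | HR |
|---|---|---|---|
| A (1,200 trials, error about 1 point) | 0.3 | 82% v 82% | 0.69 v 0.68 |
| A | 0.5 | 78% v 83% | 0.70 v 0.67 |
| B (2,000 trials, error about 0.9 points) | 0 | 81.0% v 83.0% | 0.687 v 0.677 |
| B | 0.3 | 81.0% v 84.2% | 0.691 v 0.674 |
| B | 0.5 | 78.8% v 84.1% | 0.701 v 0.674 |

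The gains run from 0 to about 5 points. In B, 2 points remain with no centre effect, and these come from the tumour covariates. At SD 0.5, null rejection of the unstratified test was about 3% in A and 4.5% in B. The stratified and adjusted analysis held 5.2–5.5% in B.

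**5. Low accrual**

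177 × 0.75 ≈ 133 evaluable patients, spread over 15 centres of assumed size; 133 × 0.3375 ≈ 45 events. Power unstratified v stratified by centre was 32.0% v 29.8% at SD 0 and 27.2% v 34.7% at SD 0.8.

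**The case against.** The strongest objection is one of scope. The Statistical analysis section is a short part of a journal article, and strata, pooling of small centres and the full covariate list often sit in the protocol or SAP. That would settle the matter if the article were silent. It instead names the test and prints a covariate list, and the list leaves out the one factor that the design balanced on. It does not say that centre will be ignored, so a fuller document may already resolve this. If so, the two need aligning.

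Other objections stand and limit the point:

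- A reader might infer that the plan biases the hazard ratio or makes the test invalid. It does neither. Under randomisation the unadjusted hazard ratio is a legitimate marginal quantity. Its distance from the conditional one is non-collapsibility, and null rejection stays at or below about 5%, within simulation error.
- A reader might infer that power is certainly lost. The article gives no between-centre variation, and does not say that surgeons or adjuvant practice differ between hospitals. Under Investigational medicinal product, standard care follows one cited guideline.
- The simulations in step 4 do not include the planned model adjusted for age, sex and stage, and their prognostic effects are assumed.
- A reader might take Table 1 as proof that stage is not one value per patient, since stage sums to 60+31+5+7 = 103 for 100 patients. Grade also sums to 103 (31+35+33+4), but primary/recurrent sums to 101 (61+35+5) and tumour number to 99 (59+36+4). A total below 100 cannot come from extra lesions, so the cause is not established.
- The Discussion's list of prognostic characteristics describes comparing the arms at baseline and does not define a covariate set. Age and sex from that list are already in the model.
- Having two hazard ratios does not affect the hypothesis test, which is the log-rank. Only the headline estimate is left open.

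**Conclusion.** The point holds as an improvement to a valid analysis. The stated analyses do not use the randomisation stratum, the adjusted model leaves out collected tumour factors and baseline selenium, and no hazard ratio is designated primary.

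The cost of leaving this as it is depends on quantities that the article does not give. At 525 evaluable patients, stratifying and adjusting gains about 0 to 5 power points under the assumed effects. For centre alone at 40% v 27.5%, the gain is under 1 point up to SD 0.4, about 3 points at SD 0.6 and 5.5 at SD 0.8. With the higher recurrence assumed in the second scenario it reaches about 8 points at SD 0.8, a roughly fivefold spread in hazard between centres. The hazard ratio moves toward 1 by 0.01 or less up to SD 0.4 and by about 0.035 at SD 0.8 (40% scenario). If accrual stays near 133 evaluable patients and centres do not differ, stratifying can cost about 2 points.

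**What to change.** Before unblinding:

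- Make the primary log-rank test stratified by centre, and do the same for the progression-free interval. Fix a rule for merging very small centres, which limits the possible loss under low accrual.
- Name as the primary estimate one centre-stratified Cox hazard ratio, adjusted for a short prespecified set: age, sex, stage, grade, primary/recurrent status, tumour number and baseline selenium. State that the stratified log-rank test decides the hypothesis, since its p-value and the adjusted interval can differ at the margin.
- Define one value per patient for each tumour factor, and a rule for unknowns.
- Fix in advance how the set is trimmed if events are few. It uses 9 parameters (1 age, 1 sex, 2 stage, 2 grade, 1 primary/recurrent, 1 number, 1 selenium), or 13 with an unknown category for each of the four tumour factors. With 177 events that is 177/13 ≈ 14 events per parameter; with 45 events it is about 3.5.
- Report the unstratified, unadjusted result as supportive.

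The cost is analysis wording only, because every variable is already collected. If results are pooled with the UK trial, as the Discussion intends, centre strata also keep the two trials' patients apart, provided that small centres are merged only within a trial.
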